#### Follow-up

At 28 ± 1 days after *visit 3*, participants will be followed up by telephone, or in person at the William Harvey Clinical Research Centre at the William Harvey Research Institute at Queen Mary University of London, to complete a brief questionnaire based upon specific aspects of symptoms.

### End of study definition

The study will end after the last participant completes *visit 4*. All samples will be analysed at the end of the study.

### Sample size determination and statistical analysis

In this study, we aim to recruit 98 participants, with 30 healthy volunteers in *part A* and 64 in *part B*. This sample size will empower the study to test the primary endpoint.

These numbers have been based upon our previous experience with typhoid vaccination which causes a reduction in FMD of ~ 1.5% absolute units which is a reduction of approximately 25% of the response [28]. We have previously identified sex differences in the response to typhoid vaccine, with a change from baseline of FMD of − 0.5 (SD = 2.4) in men and 2.4 (SD = 2.5) in women [29]. For *part A*, using these data, if we use a conservative effect size of 25% less than that achieved in our previously published study, 13 participants are required in each group to provide 90% power for the primary outcome. To account for potential dropouts of ~ 10%, 15 participants will be recruited into each group and thus 30 volunteers in total. For the analysis of *part A*, a linear regression model will be used to compare changes in vascular dysfunction pre- to post-vaccination between the sexes, unadjusted and adjusted for important risk factors including age, body mass index, and baseline vessel diameter.

Our unpublished preliminary data investigating the effects of dietary inorganic nitrate on vascular responses (FMD) has identified a decrease in FMD from baseline of 1.4 (SD = 1.5) with typhoid vaccine and with dietary nitrate intervention only 0.08 (SD = 1.7) [20]. Based on these data, for the primary outcome of change in FMD, 25 participants will be required in each group at an 80% power, to observe a difference between the intervention arms. To observe the differences between the sexes, 30 in each group provides a 90% power, which will also offer a > 95% power to detect a rise in [NO_2_^−^], as observed in previous studies [30]. To account for potential dropouts of ~ 10%, a total of 68 volunteers will be recruited. For the statistical analysis in *part B*, analysis of covariance (ANCOVA) will be used to compare the change in vascular dysfunction pre- to post-vaccination, between dietary nitrate and placebo control groups adjusting for pre-vaccination level, and to compare the change in plasma [NO_2_^−^] between the dietary nitrate and placebo control groups.

Personal data will be stored in a secured site file and clinical notes in a paper CRF, which will be security locked and coded. Only the direct research team will have access to the trial CRF. The subject will be given a unique, single identifier which will be used to identify data and samples. Results data will only be stored, shared, analysed, transmitted, and presented in an anonymised form. Participant experience questionnaires will be completed and stored in the secure CRF. Reasons for drop-out or deviation from protocol will be detailed in full. Data quality will be assessed upon completion of the study and stored electronically. Confidentiality will be maintained through these secure measures before, during, and after the trial. Data access will be granted only to direct study members. Upon completion of the study, a fully blinded data analysis will be undertaken by a statistician.

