### Original hypothesis

We hypothesise that the COVID-19 vaccine will induce inflammatory responses and thus endothelial dysfunction. However, we expect women to be protected against vascular dysfunction and hypothesise that dietary inorganic nitrate will attenuate the consequent vascular dysfunction following the delivery of the COVID-19 vaccine.

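### Part A inputs imply a rise in FMD that the cited typhoid-vaccine falls cannot be squared with, and 13 per sex does not give 90% power from those inputs

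*Protocol article*

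**What the plan says.** All planning figures are in the section on sample size determination and statistical analysis.

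- **General premise.** The numbers rest on experience with typhoid vaccine, said to lower FMD by about 1.5% "absolute units which is a reduction of approximately 25% of the response".
- **Part A inputs.** From a separate cited typhoid-vaccine study: "change from baseline of FMD of − 0.5 (SD = 2.4) in men and 2.4 (SD = 2.5) in women".
- **Part A effect and size.** The effect is discounted: "if we use a conservative effect size of 25% less than that achieved in our previously published study". The result is that "13 participants are required in each group to provide 90% power for the primary outcome", raised for dropout: "To account for potential dropouts of ~ 10%, 15 participants will be recruited into each group and thus 30 volunteers in total".
- **Part B input.** A fall of 1.4 (SD 1.5) with typhoid vaccine, against 0.08 (SD 1.7) with nitrate. The same paragraph says that 30 per group gives 90% power for differences between the sexes.

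Under the original hypothesis, the COVID-19 vaccine is expected to cause endothelial dysfunction, and "we expect women to be protected against vascular dysfunction". The Part A primary endpoint is the between-sex comparison of the change in FMD. The section states neither alpha nor whether the test is one- or two-sided.

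**The concern.** Two things do not fit.

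First, the direction. The section presents typhoid vaccine as a stimulus that lowers FMD, and two of its three sets of figures (about 1.5 and 1.4) say so. The third, which sizes Part A, has FMD hardly falling in men and rising by 2.4 in women. Read plainly, protection from a fall means little change in women, and the article nowhere says that a rise is expected. The women's value supplies most of the planning difference and is the one that sits oddly with the rest.

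Second, the sample size. Even with the printed values taken at face value, the 25% discount and the SDs do not lead to 13 per sex for 90% power.

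What is at stake is how Part A will be read. If its power is believed to be 90%, a null result will be taken as good evidence against a sex difference of the planned size. At the power that the inputs support, it would be much weaker evidence.

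**Working it through.** **Inputs** (sample-size section): men -0.5, SD 2.4; women +2.4, SD 2.5; 25% reduction; 13 per sex before and 15 after the dropout allowance; quoted falls of about 1.5 and 1.4. **Assumed**, because not stated: alpha 0.05, with both two-sided and one-sided tests tried; unadjusted two-sample comparison; equal groups.

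**1. Direction**

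- Equal-sex mean: (-0.5 + 2.4)/2 = +0.95.
- With a share p of women, the mean is -0.5 + 2.9p. Setting this to -1.5 gives p = -1.0/2.9 = -0.34; setting it to -1.4 gives p = -0.9/2.9 = -0.31. Both are impossible, since every real mix lies between -0.5 and +2.4.
- Planning difference: 2.4 - (-0.5) = 2.9. The women's rise supplies 2.4/2.9 = 83% of it.

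**2. Does the direction alter Part A power?**

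Moving the mean from +0.95 to -1.5 is a shift of -2.45 in both sexes: men -2.95, women -0.05. The difference is still 2.9, so power is unchanged. The 1.5 figure does not enter the Part A calculation.

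**3. Reproducing 13 per sex**

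- Pooled SD = sqrt((2.4² + 2.5²)/2) = 2.45.
- Planned effect = 0.75 × 2.9 = 2.175.
- Normal approximation, two-sided 0.05, 90% power: n = 2 × (1.960 + 1.282)² × 2.45² / 2.175² = 26.7, so 27 per sex. The noncentral t calculation gives 27.67, so 28.
- Standard error at 13 per sex = 2.45 × sqrt(2/13) = 0.961, and 2.175/0.961 = 2.26. Normal-approximation power is 62%; by noncentral t it is 58%.

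Noncentral t results:

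| Difference | Test | Power, 13 per sex | Power, 15 per sex | n per sex for 90% |
|---|---|---|---|---|
| 2.175 (stated rule) | two-sided | 58% | 65% | 28 |
| 2.175 | one-sided | 71% | 77% | 23 |
| 2.9 (no reduction) | two-sided | 82% | 88% | 17 |
| 2.9 | one-sided | 90% | 94% | 13 |

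Of these readings, only the last reproduces 13, and it leaves out the 25% reduction that the section says was applied. The dropout step is correct: 13/0.90 = 14.4, so 15. The Part B figure of 30 per group for a sex difference at 90% is close to the 28 found here for 2.175, which makes 13 harder to explain.

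**4. If the women's value is wrong** (assumptions for illustration only; two-sided; 13 and 15 per sex)

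- Difference 1.9, were the women's change -2.4: 48% and 54%.
- Difference 1.5, were men to fall 1.5 and women not change: 32% and 37%.

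**The case against.** The strongest reply is that Part A tests a contrast. Disagreement about the average response says nothing about the difference between the sexes, and step 2 shows that a common shift leaves power untouched. That stands. It also stands that the three sets of figures come from different cited studies, so they may disagree without any of them being misprinted, and that a rise in women is not strictly incompatible with their being protected.

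A reader might go further and infer that, on the section's own fall of 1.5 with women unaffected, Part A has only about one chance in three of success. The article does not support this. It gives no sex composition for the 1.5 figure and does not assign it to men. If 1.5 is instead an equal-sex average and women do not change, men fall by 3.0, and the difference of 3.0 slightly exceeds the printed 2.9. A reader might also infer that the sign of "2.4 (SD = 2.5) in women" is a misprint. That cannot be settled without the cited source. Nor is it true that no reading yields 90% at 13 per sex, because the undiscounted difference tested one-sided does.

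What survives is that the section sets the figures side by side as experience with one stimulus and does not reconcile them. The shortfall at 2.175 is independent of the direction question and is not answered by any of these replies.

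**Conclusion.** The point holds in two separate parts.

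1. The Part A inputs cannot be reconciled, for any mix of the sexes, with the falls of about 1.5 and 1.4 in the same section. This shows an unexplained inconsistency and does not show which figure is wrong. It matters because the value in doubt, the women's +2.4, drives the planning difference; it does not in itself lower Part A power.

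2. The 90% at 13 per sex does not follow from the printed inputs. With the stated 25% reduction, power is about 58% at 13 and 65% at 15 per sex two-sided, or 71% and 77% one-sided; 90% needs 28 per sex two-sided. This rests on alpha 0.05, the printed SDs and an unadjusted comparison. The planned adjusted regression might gain some precision, but the article gives no figure for that and does not rely on it in the calculation.

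**What to change.** - Check the sex-specific changes, including the sign of the women's value, against the cited source. Correct them, or state plainly that women's FMD rose.
- Add a sentence reconciling them with the falls of about 1.5 and 1.4, and say how a rise in women relates to the hypothesis of protection.
- State the alpha and sidedness used, and restate Part A power for 13 to 15 per sex. If the printed values stand, this is about 58% to 65% two-sided.
- If a smaller difference is shown, such as 1.5 or 1.9, label it as an assumption.

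The cost is one source check and revised wording, with a less favourable stated power. No extra participants are asked for: according to the trial status section, all 98 have completed the baseline visit. The correction should be made before the primary analysis, so that Part A is interpreted against its actual power.

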**Methods:**

DiNOVasc-COVID-19 is a double-blind, randomised, single-centre, placebo-controlled clinical trial. A total of 98 healthy volunteers (49 males and 49 females) will be recruited. Participants will be randomised into 1 of 2 sub-studies: *part A* or *part B*. *Part A* will investigate the effects of sex on vascular and inflammatory responses to the COVID-19 vaccine. *Part B* will investigate the effects of sex and dietary inorganic nitrate on vascular and inflammatory responses to the COVID-19 vaccine. In *part B*, participants will be randomised to receive 3 days of either nitrate-containing beetroot juice (intervention) or nitrate-deplete beetroot juice (placebo). The primary outcome for both sub-studies is a comparison of the change in flow-mediated dilatation (FMD) from baseline after COVID-19 vaccination. The study has a power of > 80% to assess the primary endpoint. Secondary endpoints include change from baseline in inflammatory and leukocyte counts and in pulse wave analysis (PWA) and pulse wave velocity (PWV) following the COVID-19 vaccination.

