**Fig. 2 Fig2:**
[figure not shown]
SPIRIT figure. Summary SPIRIT figure showing the visit structure and events during the clinical study

*Part A:* 15 men and 15 women will be randomised into *part A*. This part of the study will recruit equal numbers of men and women to compare the influence of biological sex on inflammatory responses and vascular function following the COVID-19 vaccine.

*Part B*: 34 men and 34 women will be randomised into *part B*. In this study, we will recruit equal numbers of men and women and make comparisons of the effects of dietary inorganic nitrate and sex on vascular function and inflammatory responses. After randomisation into *part B*, participants will undergo further randomisation to receive either 70 mL of a nitrate-containing beetroot juice (5–6 mmol, James White Drinks Ltd., UK, Beet It^®^ Sport Nitrate 400 Shot) or nitrate-deplete placebo control.

Baseline measurements of BP, PWA, PWV, FMD, blood, urine, and saliva will be taken at *visit 2*. Participants randomised to *part B* will begin taking a daily dose of the beetroot juice 2 days before receiving their COVID-19 vaccination and consume 3 consecutive daily doses. The last dose will be taken on the morning of the vaccine. All participants will receive their COVID-19 vaccination on the morning of *visit 3* and return to the clinical research facility to undergo repeat measurements of BP, PWA, PWV, FMD, blood, urine, and saliva 8 ± 2 h after the vaccine. *Visit 4* will occur 28 ± 1 days after delivery of the vaccine, at which point participants will be asked to complete a bespoke experience questionnaire. This questionnaire is bespoke and has been tailored to capture specific aspects of symptoms before and after the COVID-19 vaccination and scored from 0 to 10. These include general health, anxiety and stress, fatigue, and muscle/joint pain. We have also incorporated a rating on the experience of the intervention/placebo and included yes/no questions for whether the juice intervention/placebo was easily incorporated into their daily routine and whether the participant would be keen to continue the intervention as a lifestyle measure if found to be beneficial.

Patients will be recruited throughout all waves of the COVID-19 pandemic. Timing of when COVID-19 vaccination and previous COVID-19 infection will be obtained, to permit exploratory analyses of differences between COVID-19 waves and/or the presence of previous COVID-19 infections.

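### Part A's 13 per sex does not give 90% power at its own conservative effect: the stated inputs give about 58% (two-sided 5%) to 71% (one-sided 5%)

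*Protocol article*

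**What the plan says.** The protocol article, under Sample size determination and statistical analysis, bases Part A on an earlier typhoid-vaccine study, "with a change from baseline of FMD of − 0.5 (SD = 2.4) in men and 2.4 (SD = 2.5) in women". It then plans on "a conservative effect size of 25% less than that achieved in our previously published study" and concludes that "13 participants are required in each group to provide 90% power for the primary outcome". The number is raised for losses: "To account for potential dropouts of ~ 10%, 15 participants will be recruited into each group and thus 30 volunteers in total".

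The Part A primary endpoint (Primary endpoints) is the comparison of the sexes on change in FMD after vaccination. The planned analysis is a linear regression, both unadjusted and adjusted for age, body mass index and baseline vessel diameter. No significance level or sidedness is given for Part A. The abstract says of the study as a whole: "The study has a power of > 80% to assess the primary endpoint".

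**The concern.** The means, SDs, reduction factor, sample size and power all stand in one paragraph, so the claim can be checked directly. A standardised effect of about 0.89 with 13 per group is well short of 90% power under the usual conventions.

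Part A's FMD comparison is a named primary endpoint. A 90% claim tells readers that a true difference of the planned size would be missed one time in ten. If the true miss rate is nearer four in ten (two-sided) or three in ten (one-sided), a non-significant Part A result carries much less weight against a sex difference than the stated power implies.

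**Working it through.** **Inputs (Sample size determination and statistical analysis)**
- Change in FMD: men −0.5 (SD 2.4), women +2.4 (SD 2.5). Difference = 2.4 − (−0.5) = 2.9.
- Pooled SD with equal groups = √[(2.4² + 2.5²)/2] = √[(5.76 + 6.25)/2] = √6.005 = 2.45.
- Reduced effect = 0.75 × 2.9 = 2.175. Standardised: 2.175/2.45 = 0.89 (unreduced: 2.9/2.45 = 1.18).
- Stated: 13 per sex evaluable, 15 recruited, 90% power.
- Assumption: the test is at the 5% level, two-sided or one-sided, since neither is stated for Part A.

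**Method.** The unadjusted regression on sex is a two-sample t-test. Power comes from the noncentral t distribution with 2n − 2 degrees of freedom and noncentrality δ/(SD × √(2/n)).

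**Reproducing the stated figure.** At δ = 2.9 and n = 13 the noncentrality is 2.9/(2.45 × √(2/13)) = 3.02. The one-sided 5% critical value on 24 df is 1.711 and power is 90.1%. So 13 at 90% can be reproduced, but only without the 25% reduction and with a one-sided 5% test (the same critical value as two-sided 10%). With the two-sided 5% critical value of 2.064, power at 2.9 is 82.5%, and 13 is then the sample size for 80%, not 90%.

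**At the stated planning effect.** With δ = 2.175 and n = 13 the noncentrality is 2.175/(2.45 × √(2/13)) = 2.26.

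| Difference | Test | Power, 13 per sex | Power, 15 per sex | n per sex for 80% | n per sex for 90% |
|---|---|---|---|---|---|
| 2.175 | two-sided 5% | 58% | 65% | 21 | 28 |
| 2.175 | one-sided 5% | 71% | 77% | 17 | 23 |
| 2.9 | two-sided 5% | 82.5% | 88% | 13 | 17 |
| 2.9 | one-sided 5% | 90.1% | 93.5% | 10 | 13 |

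**Sensitivity at 2.175.** Using SD 2.4 or 2.5 alone, or a normal approximation, moves two-sided power with 13 per sex only between 57% and 64%, and one-sided power between 70% and 75%. The n for 90% ranges from 21 to 29 per sex over all these variants. None gives 13.

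**Smallest difference detectable.** With 13 per sex at two-sided 5%, 90% power is reached at a difference of 3.25, which is larger than the 2.9 seen in the earlier study.

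**Which convention is likelier.** Part B's nitrate inputs are decreases of 1.4 (SD 1.5) and 0.08 (SD 1.7): difference 1.32, pooled SD √[(2.25 + 2.89)/2] = 1.60. A two-sided 5% t-test with 25 per group gives 81%, and 25 is the smallest n that reaches 80%. This matches the article's Part B figure and points to two-sided 5%, but does not settle it for Part A.

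**Dropout step.** 13/(1 − 0.10) = 14.4, rounded up to 15. This step is correct.

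**The case against.** - **Sidedness is open.** Alpha and sidedness are not stated for Part A, and the Original hypothesis section is directional, expecting women to be protected. This stands: 58% should not be given without its assumption, and the range is 58% to 71%. It does not rescue 90%.
- **Adjustment may add power.** An adjusted model is also planned. Ignoring lost degrees of freedom, an R² of 0.2 to 0.3 would bring two-sided power with 15 per sex to about 75–80% at 2.175. Reaching 90% with 13 needs the residual SD to fall from 2.45 to about 1.64, an R² of 1 − (1.64/2.45)² ≈ 0.55. The article claims no such gain, but the figures above should be labelled unadjusted.
- **The faulty item is not identified.** It could be the 25% wording, the sidedness, the power level or a printed input. This stands, and it is why the fix asks first for the effect and test actually used.
- **The 30-per-group sentence.** A reader might infer that "To observe the differences between the sexes, 30 in each group provides a 90% power" contradicts 13. The documents do not support that. The sentence sits in the Part B paragraph and names no effect of its own. At two-sided 5%, 30 per group gives 92% at 2.175 but also 88% on Part B's nitrate inputs, so its source cannot be told.
- **The abstract.** A reader might call its power statement false for Part A. It names no effect, and at the unreduced 2.9 it holds: 82.5% with 13 per sex and 88% with 15. It fails only at the reduced effect.

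**Conclusion.** The stated power for Part A's primary endpoint does not follow from the stated inputs. At 2.175 points with pooled SD 2.45, 13 per sex gives 58% (two-sided 5%) to 71% (one-sided 5%), and 15 per sex gives 65% to 77%. The 90% claim would need 28 or 23 per sex. No convention tried that keeps the 25% reduction reaches 90% with 13. The result rests on the printed means and SDs, an unadjusted comparison and a 5% level. The choice of sidedness changes the size of the shortfall, not its existence. The statement should be corrected, because it is the headline power for a named primary endpoint.

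**What to change.** In the sample size section, state alpha, sidedness and the effect used for Part A. Then restate the unadjusted power. At two-sided 5% and a difference of 2.175, it is about 58% with 13 evaluable per sex and 65% with 15; at the unreduced 2.9, it is about 82% and 88%. Add that 3.25 points is the smallest difference detectable with 90% power with 13 per sex. If a one-sided test was intended, say so and give the one-sided figures from the table instead. In the abstract, qualify the claim of more than 80% power as holding for Part A only at the unreduced effect.

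No participants need be added. Trial status reports that all 98 have had their baseline visit, so the correction affects reporting and interpretation only. The cost is wording, and a stated power that is less favourable.

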### Randomisation and blinding process

A total of 98 healthy volunteers will be recruited. *Part A* is an observational study in which 15 males and 15 females will be recruited. *Part B* is a double-blind, randomised, placebo-controlled clinical trial and will enrol 34 males and 34 females. Randomisation into *parts A* and *B* will occur in a 1:2 fashion using block randomisation, such that recruitment occurs over a similar timespan.

In *part B*, 1:1 block randomisation will be used to allocate participants to nitrate-containing beetroot juice or nitrate-deplete beetroot juice (placebo). The treatment assignment of the volunteers will remain blinded until the end of the study, at which point the study will be unblinded. If emergency unblinding is required, the chief investigator will be informed. A list of the unblinded treatment allocations will be stored in a secure location at the William Harvey Clinical Research Centre and be available at all times.

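### Part A's primary sex comparison has about 58% power on its own inputs, not the stated 90%, and leaves out the Part B placebo arm, which could bring it to about 90%

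*Protocol article*

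**What the plan says.** All points are from the Protocol article.

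- **Endpoint.** Under Primary endpoints, Part A compares the change in FMD after vaccination between men and women.
- **Model.** Under Sample size determination and statistical analysis, the model is introduced for the analysis of Part A: "a linear regression model will be used to compare changes in vascular dysfunction pre- to post-vaccination between the sexes". It is run unadjusted and adjusted for age, body mass index and baseline vessel diameter.
- **Size.** The same section takes earlier typhoid-vaccine data, "0.5 (SD = 2.4) in men and 2.4 (SD = 2.5) in women" (the men's value carries a minus sign), and then shrinks the difference: "if we use a conservative effect size of 25% less than that achieved in our previously published study". The number it draws from this is given as follows: "13 participants are required in each group to provide 90% power for the primary outcome". It then adds: "To account for potential dropouts of ~ 10%, 15 participants will be recruited into each group and thus 30 volunteers in total".
- **Allocation between parts.** Under Randomisation and blinding process, assignment to Parts A and B "will occur in a 1:2 fashion using block randomisation", so that both recruit over a similar period. That section calls Part A observational and Part B a double-blind placebo-controlled trial with 1:1 allocation.
- **Part B.** Under Study design and intervention, "34 men and 34 women will be randomised into" Part B. All participants in both parts are vaccinated on the morning of visit 3 and have FMD repeated 8 ± 2 h later.
- **Sex in Part B.** Part B is also meant to compare the sexes, and the sample size section gives that comparison its own number: "To observe the differences between the sexes, 30 in each group provides a 90% power". The ANCOVA described for Part B compares nitrate with placebo and names no sex term.

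**The concern.** Two things go together. First, the stated power for one of the trial's primary comparisons looks too high for the effect and SD given. At that size, a real sex difference as large as the one planned for would be missed about four times in ten.

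Second, data that bear directly on the same question are left out. Part B placebo participants come from the same randomised pool, over the same period, with the same visits and FMD method. They receive the vaccine and no active nitrate. The male-female contrast among them is a no-nitrate sex comparison after vaccination, which is what Part A asks. If placebo splits evenly by sex, that is about 17 per sex against 15 per sex in Part A, so more than half of the no-nitrate information on sex lies outside the primary analysis.

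**Working it through.** **Inputs from the sample size section**
- Change in FMD: men −0.5 (SD 2.4), women 2.4 (SD 2.5). Difference = 2.4 − (−0.5) = 2.9.
- Pooled SD = √((2.4² + 2.5²)/2) = 2.45.
- Planned difference, 25% smaller: 0.75 × 2.9 = 2.175.
- Dropout about 10%.

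**Assumed:** 5% alpha, two-sided, with one-sided as a variant. The article states neither.

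**Step 1. Try to reproduce 13 per sex for 90% power.**
Normal approximation: n = 2(z_α + z_β)² SD²/δ². Exact figures use the noncentral t.

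| Difference | Test | n per sex for 90%: normal / t | Power at 13 per sex (t) |
|---|---|---|---|
| 2.175 | two-sided | 27 / 28 | 58.4% |
| 2.175 | one-sided | 22 / 23 | 71.0% |
| 2.9 | two-sided | 16 / 17 | 82.5% |
| 2.9 | one-sided | 13 / 13 | 90.1% |

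For the first row, the normal approximation is 2 × (1.960 + 1.282)² × (2.45/2.175)² ≈ 26.7, so 27. Among these variants, 13 appears only with the unreduced difference and a one-sided test, which contradicts the stated 25% reduction. The dropout step is correct: 13/0.9 = 14.4, so 15.

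**Step 2. Part A alone, difference 2.175, two-sided.**
- 13 per sex: SE = 2.45 × √(2/13) = 0.961; noncentrality 2.175/0.961 = 2.26; df 24; power 58.4%. 95% CI half-width = 2.064 × 0.961 = 1.98.
- 15 per sex (no dropout): power 65.1%.

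**Step 3. Part A plus Part B placebo, with a term for part.**
- Part B placebo: 68/2 = 34, about 17 per sex if even. 17 × 0.9 = 15.3, so 15 completers.
- Total 13 + 15 = 28 per sex; df = 56 − 3 = 53.
- SE = 2.45 × √(2/28) = 0.655; noncentrality 2.175/0.655 = 3.32; power 90.3%.
- 95% CI half-width = 2.006 × 0.655 = 1.31, which is 34% narrower than 1.98.
- No dropout (15 + 17 = 32 per sex): power about 94%.
- Stratification of placebo by sex is not stated. With 10 completers of one sex and 20 of the other on placebo, the information weights are 13 × 13/26 = 6.5 and 10 × 20/30 = 6.67. SE = 2.45/√13.17 = 0.675, and power is 88.5%.

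**Step 4. The Part B sex statement.**
At 2.175 and SD 2.45, 30 per sex gives 92.2%, close to the stated 90%. So one section attaches 90% power to a sex difference at both 13 and 30 per group, and only the larger number fits the reduced effect. With about 17 per sex on placebo, 30 per sex in Part B can be reached only by counting participants on nitrate.

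**Step 5. What a sex-by-part check can show.**
SE of the difference in sex effects = 2.45 × √(2/13 + 2/15) = 1.31; df 52. The 95% half-width is about 2.6. If the sex effect differed between parts by the whole 2.175, power to detect it would be about 37%.

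**The case against.** *The trial does study sex outside Part A.* A reader might infer that the sex question is answered from Part A alone and that the placebo arm plays no part in it. The documents do not support that. Part B has a stated aim of comparing the sexes and a number for it. What stands is narrower: nothing brings the placebo arm into Part A's primary comparison. The Part B number mixes in nitrate-treated participants, and the Part B ANCOVA names no sex term.

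*Analysing a sub-study in its own participants is legitimate, and a supporting pooled analysis could sit in a document not shown.* That is fair as far as pooling goes. But the article fixes both the analysis set and its power, and that power does not follow from its inputs. The sample-size error stands whether or not pooling is adopted.

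*Part A takes no juice and is labelled observational.* A term for part absorbs a shift in mean FMD change. It does not absorb a juice effect that differs by sex. This objection stands. It is tempting to say that a sex-by-part check would settle the matter, but Step 5 shows that it cannot.

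*The change is late, and the placebo arm would serve two primary comparisons.* Trial status reports that all 98 baseline visits are done and six participants await vaccination. The treatment code stays blinded until the end of the study and the primary analysis starts after the last visit, so there is still room to pre-specify. Sex, however, is not hidden by the treatment code, so the change must also precede any look at FMD change by sex. Using the placebo arm twice makes the two results correlated and should be stated.

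**Conclusion.** The point holds for Part A's primary comparison. On the protocol's own difference and SD, 13 per sex gives about 58% power two-sided (71% one-sided), not 90%. Two-sided, 90% needs about 28 per sex. Part A plus the Part B placebo arm supplies about that number from participants already in the trial, giving about 90% power and a half-width of 1.31 against 1.98.

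The 58% is a recalculation, not a figure in the article. It rests on the 25% smaller effect, SD 2.45 and an assumed 5% alpha. The 90% rests further on about 10% dropout, a roughly even sex split on placebo, and nitrate-deplete juice leaving the sex difference unchanged.

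**What to change.** 1. Restate Part A's power as about 58% at 13 per sex and about 65% at 15, with alpha and sidedness given.
2. Before unblinding, and before any tabulation of FMD change by sex, pre-specify a regression of FMD change on sex with a term for part, in Part A plus Part B placebo. State its expected power of about 90% and the assumptions behind it.
3. Report Part A alone beside it.
4. Report the sex-by-part estimate with its confidence interval as descriptive only, and do not use it to justify pooling.
5. Say how the Part B sex comparison relates to this one, including which participants make up its 30 per group and which model term estimates it.

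The cost is a dated change to the analysis text, with no new participants or measurements. The sex result would wait for Part B unblinding, a small delay because primary analysis already waits for the last visit. The remaining price is the untestable assumption about the juice, which the Part A result beside it keeps visible.
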